### Study setting

THIN captures clinical data from general practices across the UK, holding anonymised records of approximately 6% of the UK population from 850 general practices. THIN has over 25 years of data recorded. To ensure a complete and reliable dataset, this project will capture data between January 1st, 2006, and December 31st, 2021. Preliminary counts from THIN show 530,792 patients with a TSH greater than 4 mIU/L. Preliminary counts also show 258,868 patients diagnosed with hypothyroidism within the same period. The variables that will be captured from the THIN database are as follows:

sex,diagnosed with hypothyroidism,date of diagnosis of hypothyroidism,date LT4 treatment commenced,first and last recorded LT4 dose,co-morbidities (heart disease, asthma, chronic obstructive pulmonary disease, diabetes, chronic kidney disease, rheumatoid arthritis, depression, dementia, dyslipidaemia, osteoporosis, fragility fractures).date of diagnosis of co-morbidities,current and past medications,date of death (if applicable),TSH, fT4, thyroxine (T4), triiodothyronine (T3), and free triiodothyronine (fT3) levels,date of recorded TSH, fT4, T4, T3, and fT3 levels,thyroid peroxidase antibody status,body mass index (BMI) at entry and end of the study period,blood pressure,smoking status.

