#### Inclusion criteria

Patients registered on the THIN database and aged over 50 on January 1st, 2006.Patients with a recording of TSH above 4.0 mIU/L between January 1st, 2006, and December 31st, 2021.Patients who are prescribed LT4 or receive no hormone replacement therapy. In the cohort study, patients in the treatment group will be prescribed LT4 before the end of the study period, December 31st, 2021. In the emulated target trial study, patients will initiate LT4 treatment and remain on it during a 5-year follow-up between January 1st, 2006, and December 31st, 2021. Patients in the emulated target trial study will be randomly assigned a strategy at baseline and be aware of their assignment.In the cohort study, patient follow-up ends at death, withdrawal from the database or December 31st, 2021, whichever occurs first.

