### Statistical analysis

The sample size calculation is based on the primary outcome of determining a difference in cardiovascular outcomes between patients receiving LT4 or not. The TRUST study of 737 patients aged 65 years and older found a cardiovascular outcome rate of 4.9% in the treatment group and 5.4% in the placebo group. Therefore, based on these outcome rates, for the cohort study, the minimum sample size required is 82,118 patients. Of this sample, 41,059 patients will be prescribed LT4 and 41,059 patients will not be prescribed LT4. A matching ratio of 1:4 (treatment: no treatment) will be used for the target trial emulation study. Therefore, the sample size required is 129,020 patients, with 25,804 patients prescribed LT4 and 103,216 patients not prescribed LT4. This sample size provides a power of 0.9 and alpha of 5%. In both studies, if missing data occurs, multiple imputation methods will be used if up to 40% of the data is missing [47]. Otherwise, pairwise deletion will be used.

In the target trial emulation study, the causal contrasts of interest will be intention-to-treat effect. Chi-square analysis will be used to compare the categorical characteristics of the participants in both studies, such that a p-value of less than 0.05 will be considered significant. Descriptive statistics will be presented. In both studies, the frequency of hypothyroidism diagnosis, smoking status, sex, ethnicity, and location will be given for each group. Survival analysis methods, including Cox proportional hazard models and Kaplan-Meier curves, will be fitted to compare the time to outcome between the groups. The hazard ratios with their 95% confidence intervals will be given.

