Confounding bias, immortal time bias, and information bias will be adjusted for both the cohort and target trial emulation studies [48]. In addition, selection bias and attrition bias will be adjusted for in the target trial emulation study. Confounding factors include sex, BMI, co-morbidities, and smoking status. The adjustment for confounding factors will be done using inverse probability weighting in the target trial emulation study [49]. In both studies, subgroup analysis will be done for each cardiovascular and bone health outcome and each age group (51–60, 61–70, 71–80, 81–90, 91 + years). A subgroup analysis including patients with a TSH level between 4 0.0 mIU/L and the upper limit of their age range in the TEARS study will be carried out. Another subgroup analysis of patients who have had a TSH level of 10 mIU/L or above or not will be conducted. Also, sensitivity analysis will be undertaken in both studies for different TSH thresholds, as the standard threshold can differ between laboratories. This study will perform a secondary analysis based on baseline fT4 levels, comparing patients with a low normal versus high normal levels (below and above median levels at baseline, respectively).

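### The cohort's treated group is defined by any LT4 prescription up to the end of 2021, a grouping by future exposure that conflicts with the promise to deal with immortal time bias

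*Protocol article*

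**What the plan says.** All references are to the protocol article.

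- **Eligibility** (Inclusion criteria): "Patients with a recording of TSH above 4.0 mIU/L between January 1st, 2006, and December 31st, 2021".
- **Groups** (Inclusion criteria): "Patients who are prescribed LT4 or receive no hormone replacement therapy". For the cohort the treated group is then fixed: "In the cohort study, patients in the treatment group will be prescribed LT4 before the end of the study period, December 31st, 2021".
- **End of follow-up** (Inclusion criteria): "In the cohort study, patient follow-up ends at death, withdrawal from the database or December 31st, 2021, whichever occurs first". A non-fatal outcome event is not in this list.
- **Comparison** (Statistical analysis): "Survival analysis methods, including Cox proportional hazard models and Kaplan-Meier curves, will be fitted to compare the time to outcome between the groups".
- **Immortal time** (Statistical analysis): "Confounding bias, immortal time bias, and information bias will be adjusted for both the cohort and target trial emulation studies". A reference is cited and no method is named. Inverse probability weighting is named, but only for confounding in the target trial emulation.
- **Data** (Study setting): the variables to be extracted include "date LT4 treatment commenced".

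**The concern.** The qualifying TSH can fall anywhere in a 16-year window, and so can the prescription that makes a patient treated. Membership of the treated group is therefore settled by something that happens during follow-up. Time between entry and first prescription is spent untreated, yet a fixed grouping credits it to LT4. For death, that time is event-free by construction.

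The alternative hypothesis under Study aims is that LT4 gives worse cardiovascular and bone outcomes. A bias towards apparent protection would work against finding such harm, and with a planned cohort of 82,118 patients a biased estimate would also look precise. The protocol says this bias will be adjusted for, but the exposure rule it prints is the one that creates it.

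**Working it through.** **1. Benchmark from the plan.** The planning rates are 4.9% and 5.4%, a risk ratio of 0.049/0.054 = 0.907. With a two-sided 5% test and power 0.9,

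n per group = [1.960·√(2·0.0515·0.9485) + 1.2816·√(0.049·0.951 + 0.054·0.946)]² / 0.005² = (0.6126 + 0.4005)² / 0.000025 ≈ 41,059.

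This reproduces the stated 41,059 per group. The sample size is not in question. The figure that matters here is 0.907, the contrast the cohort is sized to see.

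**2. What the exposure rule requires.** The rule asks only for a prescription before 31 December 2021. It does not require the patient to be event-free at that prescription. Two cases follow.

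- *Death.* A patient who dies first cannot later be prescribed LT4. Survival to prescription is unavoidable.
- *Non-fatal outcomes* (angina, myocardial infarction, stroke and the other cardiovascular and bone diagnoses). A patient may have the event and start LT4 afterwards. On the literal wording that patient is treated. If the analysis instead requires LT4 before the event, the situation is the same as for death.

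**3. Size when LT4 has no effect.** The document gives no time to LT4 start and no event rates by year, so the following are assumptions: 400,000 patients; constant event rate of 1%, 2% or 4% per year; 70% eventual starters; median time to LT4 of 0.5, 1, 2 or 4 years; follow-up uniform between 0.5 and 16 years; start of LT4 independent of the event. True ratio = 1. Across the 12 settings:

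| How LT4 is handled | Treated vs untreated ratio |
|---|---|
| Fixed group, LT4 must precede the event (always so for death) | 0.45 to 0.77 |
| Fixed group, LT4 after a non-fatal event also counts | 0.99 to 1.01 |
| Treated clock starts at prescription, untreated clock at TSH | 0.68 to 0.84 |
| LT4 time-varying | 0.99 to 1.03 (simulation noise around 1) |

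For the two fixed groupings, Cox hazard ratios agreed with these rate ratios to within 0.01. Immortal time made up 9% to 36% of the treated group's person-years.

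**4. One setting in full** (2% per year, median 2 years to LT4, LT4 before the event).

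- Fixed groups: treated 28,851 / 1,920,858 = 0.01502 per year; untreated 31,049 / 1,050,870 = 0.02955; ratio 0.51.
- Of the treated person-years, 493,147 precede LT4. Moving them to the untreated side gives treated 28,851 / 1,427,711 = 0.02021; untreated 31,049 / (1,050,870 + 493,147) = 31,049 / 1,544,017 = 0.02011; ratio 1.00.

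The same events are used in both lines. Only the person-time moved, and no covariate or weight entered the correction.

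**5. Sensitivity to assumptions.** A second set was run: entry uniform over 16 years, 3% loss per year, 5-year risk 5% to 20%, every patient able to start LT4 at 0.05 to 0.5 per year. The hazard ratio was 0.12 to 0.43 when LT4 must precede the event, about 1.0 when LT4 after a non-fatal event counts, and 0.99 to 1.02 with split person-time. The direction is stable; the size is not.

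**The case against.** The strongest reply is that the plan names immortal time bias, undertakes to handle it in both studies, and extracts the LT4 start date that a time-dependent analysis needs. A Cox model with LT4 as a time-varying term is still a Cox model. A condensed article may leave the method and the start of follow-up to a full protocol or analysis plan that is not shown. This stands in part: neither the unnamed method nor the unstated start of follow-up is held against the plan. What remains is the rule that is printed. A time-varying analysis would have to override it.

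A reader might infer that the rule is certain to make LT4 look protective on all three outcome families. The document does not support that. The inclusion criterion contains no event-free condition, and a non-fatal event does not end cohort follow-up. If LT4 after a non-fatal event counts as treated and starting is unrelated to the event, the null ratio is about 1. It can move either way. If death after an event prevents later prescribing, the ratio falls: it was 0.89 to 0.91 with mortality assumed at 3% per year, tripled after an event, and a slow LT4 start. If an event makes LT4 more likely, the ratio rises. That reading is still unsound, because it counts events that occurred before treatment as outcomes of treatment.

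A reader might also take 0.45 to 0.77 as the expected bias. The two sets of assumptions in the working give ranges that do not overlap, so neither is an estimate for this database.

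**Conclusion.** The point holds in this form. The cohort's treated group is defined by exposure after entry, and this conflicts with the statement that immortal time bias will be adjusted for, since a fixed ever/never grouping can be repaired only by changing how exposure and person-time are defined.

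- **All-cause mortality (objective 3):** bias towards apparent protection if fixed groups are followed from entry. The null rate ratio is about 0.45 to 0.77 under the first set of assumptions, well beyond the planning contrast of 0.907.
- **Cardiovascular and bone outcomes (objectives 1 and 2):** the same bias if LT4 must precede the event; otherwise misattribution of pre-treatment events, with a net bias that may be near zero or of either sign.

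The direction for mortality follows from the rule and from following fixed groups from entry. Every size rests on assumptions outside the document. The target trial emulation is not part of this point.

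**What to change.** Replace the ever-prescribed definition of the cohort's treated group with this rule: follow-up starts for every patient at the first eligible raised TSH; the patient contributes untreated time until the recorded LT4 start date and treated time after it; an event before LT4 counts as untreated. Fit the Cox models with LT4 as a time-varying exposure. Draw any Kaplan-Meier curves from a pre-specified landmark after index, grouping by LT4 status at that time among patients still under follow-up and event-free. Starting only the treated clock at the prescription is not enough, as the third row of the table shows.

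The cost is wording and programming. The LT4 start date and dated TSH values are already on the extraction list, and the stated sample-size arithmetic is unaffected. The landmark curves lose the events that occur before the landmark; the time-varying Cox models keep them.

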## Methods/Design

### Study aims

The study aims to evaluate whether LT4 benefits patients aged over 50 years with marginally raised TSH. The null hypothesis is that SCH patients over 50 years of age have the same bone health and cardiovascular outcomes when prescribed LT4 compared to those not prescribed LT4. The alternative hypothesis is that SCH patients aged over 50 years of age have worse bone health and cardiovascular outcomes when prescribed LT4 than those who are not prescribed LT4.

The objectives of the study are:

1) To use electronic healthcare records to undertake a cohort study comparing the cardiovascular outcomes (incident diagnosis of angina, myocardial infarction, stroke, peripheral vascular disease and stent/revascularisation procedure) between patients over 50 years of age with mildly elevated TSH levels prescribed LT4 versus those not prescribed LT4.

2) To use electronic healthcare records to undertake a cohort study comparing the bone health outcomes (incident diagnosis of osteoporosis, fragility fractures) between patients over 50 years of age with mildly elevated TSH levels prescribed LT4 versus those not prescribed LT4.

3) To use electronic healthcare records to undertake a cohort study comparing all-cause mortality outcomes between patients over 50 years of age with mildly elevated TSH levels prescribed LT4 versus those not prescribed LT4.

4) To use electronic healthcare records to undertake a target trial emulation study comparing the cardiovascular outcomes (incident diagnosis of angina, myocardial infarction, stroke, peripheral vascular disease and stent/revascularisation procedure) between patients over 50 years of age with mildly elevated TSH levels prescribed LT4 versus those not prescribed LT4 [46].

5) To use electronic healthcare records to undertake a target trial emulation study comparing the bone health outcomes (incident diagnosis of osteoporosis, fragility fractures) between patients over 50 years of age with mildly elevated TSH levels prescribed LT4 versus those not prescribed LT4.

6) To use electronic healthcare records to undertake a target trial emulation study comparing all-cause mortality outcomes between patients over 50 years of age with mildly elevated TSH levels prescribed LT4 versus those not prescribed LT4.

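### Listed as an inclusion criterion, staying on LT4 through a 5-year follow-up would select the emulation's treated arm on post-baseline events and conflict with the intention-to-treat contrast

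*Protocol article*

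**What the plan says.** Four statements in the protocol article bear on who enters the emulation and how they are analysed.

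- Inclusion criteria: in the emulated trial "patients will initiate LT4 treatment and remain on it during a 5-year follow-up between January 1st, 2006, and December 31st, 2021". The preceding sentence defines the cohort study's treated group by an LT4 prescription before the study ends.
- Inclusion criteria, next sentence: "Patients in the emulated target trial study will be randomly assigned a strategy at baseline and be aware of their assignment".
- Statistical analysis: "the causal contrasts of interest will be intention-to-treat effect".
- Study aims, objective 6: the plan is to "undertake a target trial emulation study comparing all-cause mortality outcomes between patients over 50 years of age". Objectives 4 and 5 do the same for cardiovascular and bone outcomes.

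The only explicit rule for ending follow-up is limited to the other study: "In the cohort study, patient follow-up ends at death, withdrawal from the database or December 31st, 2021, whichever occurs first". On bias, the Statistical analysis section says: "Confounding bias, immortal time bias, and information bias will be adjusted for both the cohort and target trial emulation studies". It adds that selection and attrition bias will be dealt with in the emulation. The one method it names is tied to confounding: "The adjustment for confounding factors will be done using inverse probability weighting in the target trial emulation study".

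**The concern.** An intention-to-treat contrast places patients in an arm from what is known at baseline and keeps them there whatever they do afterwards. Remaining on a drug through a 5-year follow-up is known only afterwards. If it decides who enters the LT4 arm, patients who stop LT4 early are removed, including those who stop because of an event. If five years must be completed, those who die early are removed as well. The untreated group faces no matching persistence or survival test in the text.

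The direction of the bias matters here. The study's alternative hypothesis is that LT4 patients do worse. Removing LT4 patients whose course went badly makes LT4 look safer, so real harm could be hidden in half of the six objectives.

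**Working it through.** **1. The plan's own figures.** Inputs from the Statistical analysis section: 4.9% with LT4, 5.4% without, power 0.9, alpha 5% (taken as two-sided), ratio k of untreated to treated.

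n(LT4) = [1.960·√((1+1/k)·p̄(1−p̄)) + 1.282·√(p₁(1−p₁) + p₂(1−p₂)/k)]² / (p₁−p₂)², with p̄ = (p₁+k·p₂)/(1+k).

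- k = 1: p̄ = 0.0515, n = 41,059 per arm, total 82,118, as stated.
- k = 4: p̄ = 0.0530, n = 25,804 treated and four times as many untreated, total about 129,020, as stated.

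The sample sizes are sound and not in dispute. The planned effect is a risk ratio of 0.049/0.054 = 0.907, or a hazard ratio of ln(1−0.049)/ln(1−0.054) = 0.905.

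**2. Three readings of the persistence sentence.**

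| Reading | Who is lost from the LT4 arm | Compatible with intention-to-treat? |
|---|---|---|
| Eligibility, five years completed | Early deaths and stoppers | No |
| Eligibility, on LT4 for as long as followed | Stoppers only | No |
| Target-trial strategy, not a filter | Nobody | Yes |

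**3. Size under the first reading, with no true effect.** Assumptions, none of them in the documents: constant hazards, a 5-year cardiovascular risk of 5.4% in both groups (the placebo-group rate, treated as a 5-year risk), a fraction f of cardiovascular events fatal at once, and a fraction q of events leading to stopping LT4. Other deaths and other stopping are independent of the cardiovascular event.

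- Hazard: h = −ln(0.946)/5 = 0.01110 per year. This is the rate in the unselected group.
- Share of events that survive selection: s = (1−f)(1−q).
- Events kept per eligible patient: 0.054·s.
- Person-years: event-free patients give 0.946×5 = 4.730. Patients with an event give 0.054/0.01110 − 4.730 = 0.134 per eligible patient before selection, so 0.134·s after it.
- Spurious rate ratio = [0.054·s / (4.730 + 0.134·s)] / 0.01110.

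Independent death and independent stopping cancel from this ratio.

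| Fatal events f | q = 0 | q = 20% |
|---|---|---|
| 0% | 1.00 | 0.80 |
| 10% | 0.90 | 0.73 |
| 20% | 0.80 | 0.65 |
| 25% | 0.76 | 0.61 |
| 30% | 0.71 | 0.57 |

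Worked example, f = 10%, q = 0: s = 0.9, and 0.0486/4.850 = 0.01002, so the ratio is 0.01002/0.01110 = 0.90. A simulation with 2% other-cause death and 10% LT4 discontinuation per year agrees to within 0.01 (0.90, 0.81 and 0.71 at 10%, 20% and 30% fatality with q = 0). Cardiovascular rates of 1% to 3% per year change the result little: 0.90 to 0.91 at 10% fatality and 0.76 at 25%.

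**4. Mortality under the first reading.** Five-year mortality in the LT4 arm is 0 because survival is a condition of entry. In the same simulation the unselected group has about 10% to 11%.

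**5. Under the second reading** deaths on LT4 are kept, and the bias comes only from stopping that is linked to the outcome. With q = 20% and no fatal events the ratio is 0.80; with q = 0 it is 1.00.

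**The case against.** The strongest reply is that the persistence sentence was never meant as a filter. The sentence after it speaks of a strategy assigned at random with patients aware of it, which can only describe the hypothetical trial. The two sentences then read as target-trial components: strategy, then assignment. The heading does not settle the matter, because the same block also holds the cohort's end-of-follow-up rule, which is not an eligibility criterion either. This stands as a plausible reading. A trial can assign patients to start and stay on a drug and still be analysed by intention-to-treat, so a reader who infers that the two statements clash on every reading goes too far. The clash arises only if persistence decides entry.

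The second reply is that the plan undertakes to adjust for immortal time bias and selection bias, with details left to a fuller document. That makes a deliberate survivor filter less likely. It does not cure one if it is applied: patients excluded by eligibility are not in the data set, and weighting for confounders cannot bring them back.

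Third, a reader might infer that LT4-arm mortality is certainly zero. The wording does not say that five years must be completed; someone who dies on LT4 in year two arguably remained on it during their follow-up. Nor do the documents say that the untreated group keeps early deaths and loses later starters, since its definition has no time window.

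Fourth, the cardiovascular ratios depend on assumed fatality and event-triggered stopping. The composite includes angina, peripheral vascular disease and revascularisation, so nothing in the documents supports the higher fatality values. This also stands.

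**Conclusion.** The point holds in conditional form. As placed, the sentence is an eligibility rule based on post-baseline behaviour. Used that way, it contradicts the intention-to-treat contrast and biases objectives 4 to 6 in favour of LT4. If it is meant as the target-trial strategy, the contradiction disappears, but the sentence is in the wrong place and invites a programmer to filter on it. Either way the text needs correcting before the emulation data set is built.

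The documents do not establish that the treated arm will in fact be survivor-selected, and they do not fix the size of the bias. On the stated assumptions, completing five years with about 10% of cardiovascular events fatal is enough for the artefact (0.90) to match the whole planned effect (0.905). With no fatal events and no event-triggered stopping there is no cardiovascular artefact. The mortality comparison in objective 6 is the most exposed, because it loses all meaning over five years if completion is required.

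**What to change.** - Remove the requirement to remain on LT4 through the 5-year follow-up from the inclusion criteria. If it describes the target trial's strategy, state it under that label and say that it does not select records.
- Define the arms by LT4 initiation versus non-initiation at a stated time zero, using baseline information only, with any grace period handled explicitly.
- For the intention-to-treat analysis, keep later stoppers and later starters in their original arm.
- Give the emulation its own end of follow-up: outcome, death, deregistration, 5 years or 31 December 2021, whichever is first.
- Replace the statement on random assignment with one saying that patients are classified by observed initiation and that randomisation is emulated by weighting.
- If a sustained-use effect is wanted, name it as a separate per-protocol contrast, with censoring at deviation and censoring weights.

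Sequential trials or cloning with censoring and weighting are possible implementations; the correction does not depend on either. The cost is protocol wording and programming. The LT4 start date, dated TSH values and date of death are already among the variables listed under Study setting. The per-protocol option would also need dated LT4 prescriptions to identify stopping; the listed current and past medications may supply these, and this should be confirmed.

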### Study design

A retrospective cohort study and a target trial emulation study will be conducted using electronic health records held in The Health Improvement Network (THIN) database.

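### The inclusion criteria give the emulation a random, open assignment that past records cannot contain, and the adjoining rule on staying on LT4 does not fit the intention-to-treat contrast

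*Protocol article*

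**What the plan says.** All references are to the protocol article.

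- **Study design:** "A retrospective cohort study and a target trial emulation study will be conducted using electronic health records". **Study setting** describes the source as "holding anonymised records of approximately 6% of the UK population from 850 general practices" and says that "this project will capture data between January 1st, 2006, and December 31st, 2021".
- **Inclusion criteria**, on treatment in the emulation: "In the emulated target trial study, patients will initiate LT4 treatment and remain on it during a 5-year follow-up". The next sentence, on assignment: "Patients in the emulated target trial study will be randomly assigned a strategy at baseline and be aware of their assignment".
- **Study aims**, objectives 4 to 6: the emulation compares patients prescribed LT4 with patients not prescribed it.
- **Statistical analysis:** the emulation is matched 1:4 and needs 129,020 patients, 25,804 prescribed LT4 and 103,216 not. It also says that "the causal contrasts of interest will be intention-to-treat effect" and that "The adjustment for confounding factors will be done using inverse probability weighting in the target trial emulation study". Immortal time bias is to be handled in both studies, and selection and attrition bias in the emulation.

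**The concern.** An emulation has two layers: the randomised trial one would have liked to run, and what is done with the records in its place. Random, open-label assignment belongs to the first layer. Here it stands among the eligibility criteria as something that will happen to the patients whose records are analysed. It is wrong as written.

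The arm is what an intention-to-treat contrast rests on. The arm must be fixed at time zero and must not depend on what happens afterwards. The Inclusion criteria contain two emulation-specific statements bearing on the arm. One cannot be carried out. The other, if used to decide who belongs to the treated arm, depends on five years of follow-up. At stake are whether the arms can be formed without looking ahead, and whether readers are told that the design has a protection from confounding that it lacks.

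**Working it through.** **1. Sample size, to see whether the defect reaches it.** Inputs from Statistical analysis: risks of 4.9% (LT4) and 5.4% (no LT4), power 0.9, alpha 5%. Two-sided testing is assumed, because the article does not state sidedness and the one-sided version does not reproduce the figures. With k untreated patients per treated patient and p̄ = (p1 + k·p2)/(1 + k):

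n(LT4) = [1.960·√((1 + 1/k)·p̄(1 − p̄)) + 1.2816·√(p1(1 − p1) + p2(1 − p2)/k)]² / (p2 − p1)²

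- k = 1, p̄ = 0.0515: (0.61261 + 0.40054)² / 0.005² = 41,059.04 per group. The plan has 41,059 per group, 82,118 in total.
- k = 4, p̄ = 0.053: (0.49093 + 0.31226)² / 0.005² = 25,804.5 treated. The plan has 25,804, with 4 × 25,804 = 103,216 untreated and 129,020 in total.

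Both figures reproduce. They depend on the number of patients with and without recorded LT4 and do not use the assignment sentence, so correcting its wording leaves them unchanged.

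**2. Random, open assignment against the data source.** The study is retrospective and the records are anonymised, ending on 31 December 2021. Treatment was started or not in ordinary care. The study can neither allocate a strategy nor tell a patient about one, so the sentence cannot be true of the emulation.

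**3. Random assignment against the analysis.** The objectives and the sample size define groups by whether LT4 was prescribed. Weighting for sex, BMI, co-morbidities and smoking is planned because those groups are expected to differ at baseline. Random assignment would leave no systematic baseline confounding to remove. The two descriptions cannot both hold for the same patients.

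**4. The five-year sentence against intention-to-treat.** Suppose membership of the treated arm requires starting LT4 and remaining on it for five years.

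- A patient who starts at baseline and stops in year 2 is removed or reclassified because of a later event. An intention-to-treat contrast would keep that patient in the LT4 arm.
- A patient who starts at baseline and dies in year 2 has not remained on LT4 for five years and would not qualify. Under a strict reading no death within five years could occur in the treated arm, whatever the drug does. That is immortal time, and it bears directly on objective 6 (all-cause mortality).
- For cardiovascular and bone outcomes, selecting patients who survive and persist with treatment can also distort the comparison. The documents give no persistence or discontinuation rates, so neither its direction nor its size can be calculated.

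**5. Result.** Neither sentence can serve as the emulation's arm rule. The rule that the rest of the plan implies, recorded prescribing with adjustment, is usable, but the Inclusion criteria contradict it.

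**The case against.** The strongest reply is that this is one misplaced sentence. The Study aims, the general inclusion criterion on LT4 or no hormone replacement, the 1:4 matching and the weighting all point to groups formed from recorded LT4. Analysts would follow those. This stands: the assignment sentence is not the only statement about arms, and the intended analysis can be guessed.

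A reader might go further and infer that the emulation is bound to return a null result. If labels were drawn at random, both arms would have the same expected risk: at a 1:4 mix, 0.2 × 4.9% + 0.8 × 5.4% = 5.30% in each. That is true by construction for any label unrelated to treatment. It does not measure harm from this plan, since the plan's other sections leave no realistic route to drawing such labels. The documents do not support the inference. Nor do they propose to report the emulation as a randomised study. It is called an emulation throughout, and the Discussion looks to a later randomised trial for confirmation.

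The five-year sentence also has a fair reading. As part of the target trial, a strategy of starting and continuing LT4 can be compared by intention-to-treat, because assignment is fixed whatever patients do later. That does not rescue its place among the emulation's inclusion criteria, where it decides who is counted.

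Finally, a condensed article may leave the details of time zero and of any initiation window to a fuller document, and it does promise to deal with immortal time bias. Both points are fair, and the absence of such details is not the complaint. The complaint is that two rules that are stated contradict the plan and work against that promise.

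**Conclusion.** The concern holds as a misstated assignment rule. Random, open assignment is impossible in these records and contradicts the recorded-treatment groups, the matching and the weighting. The neighbouring five-year condition, applied as an arm definition, uses post-baseline information, does not fit the intention-to-treat contrast and invites immortal-time and selection bias.

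No numerical bias can be attached. It would depend on whether the five-year condition is enforced and on stopping and death rates that the documents do not give. The one consequence that follows by logic is the absence of deaths within five years in the treated arm under the strict reading. The sample sizes stand.

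This is a correction worth making before analysis. It does not invalidate the design. It assumes that the intended emulation groups patients by recorded LT4, as the objectives and the sample size indicate.

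**What to change.** 1. Move the random-assignment sentence out of the emulation's inclusion criteria, or label it plainly as the target trial's specification. Treat the start-and-continue sentence the same way.
2. State the emulation's rule: patients are classified at a defined time zero by recorded LT4 initiation or non-initiation, and stay in that group regardless of later continuation. Assignment is treated as random only conditional on measured baseline confounders, through the planned matching and weighting.
3. Describe the estimate as an observational analogue of intention-to-treat.
4. If initiation is allowed within a grace window after time zero, name a method that avoids immortal time and reconcile it with the 1:4 matching. Cloning patients to both strategies, censoring on departure and weighting is one option. It starts with arms of equal size, so its relation to the 1:4 ratio and the 129,020 total would need explaining.

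**Cost:** Steps 1 to 3 are wording, with no new data and no change in sample size. Step 4, if used, adds the method's code and a sensitivity analysis on the length of the window.
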